### 3.9. Secondary Outcomes

#### 3.9.1. Physical Activity Levels

These will be assessed by the International Physical Activity Questionnaire (IPAQ) [27], which has shown good test–retest reliability, achieving an intraclass correlation coefficient of 0.70 in Colombian adults [28]. The IPAQ provides detailed insights into the time spent walking or engaging in moderate- or vigorous-intensity activities as well as in sedentary behaviors.

#### 3.9.2. Anxiety and Depression Scale

The Hospital Anxiety and Depression Scale (HADS) [29] will be used for assessment. The reliability of the HADS was confirmed in a primary care setting in Colombia, with Cronbach’s α at 0.85 and McDonald’s ω at 0.82; confirmatory factor analysis supported a satisfactory two-factor structure [30]. This self-administered scale, commonly used in non-psychiatric hospital settings and primary care, consists of 14 items. Each item offers four response options, scored from 0 to 3. The total score ranges from 0 to 21, with 0 to 7 indicating a normal range, while scores from 8 to 21 are indicative of borderline or clinical concerns about anxiety or depression.

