Another key expectation is the positive impact of the intervention on mental health. Although we acknowledge that increased awareness could potentially lead to anxiety if not properly managed, the structure of our intervention is designed to provide support and reassurance, thereby mitigating negative emotional impacts and promoting mental wellbeing. Therefore, we predict a reduction in anxiety and depression scores, as measured by the HADS, especially in the intervention group. The supportive nature of the intervention, coupled with regular information dissemination about cardiovascular health, is expected to alleviate participants’ stress and anxiety. Research has demonstrated that in anxious individuals, having more knowledge about their condition and prognosis can help modulate their behaviors in a positive way. For instance, de la Maza et al. (2015) [36] have shown that an educational program for parents of children with cancer not only increased their knowledge about the disease but also reduced their anxiety levels. Similarly, Çankaya and Şimşek (2021) [37] and Khalilzadeh Ganjalikhani et al. (2019) [38] support the notion that health education can effectively reduce anxiety, improve self-efficacy, and enhance the overall quality of life. Furthermore, an improvement in the quality of life, as reflected in the SF-36 scores, is also anticipated. The comprehensive educational content, which includes aspects like diet, exercise, and medication management, is likely to contribute to this overall enhancement in life quality.

An important aspect of this study will be the evaluation of the intervention’s sustained impact over time. We expect that the improvements in knowledge, physical activity, mental health, and quality of life will not only be evident immediately after the intervention but will also persist during the follow-up assessments at 3, 6, and 12 months. High adherence to the intervention is also anticipated, given the convenience and familiarity of the WhatsApp platform. The ease of receiving and interacting with educational content through a widely used app is expected to foster consistent participant engagement.

In conclusion, this study is poised to offer significant insights into the effectiveness of using a popular digital platform for health education in CR. The anticipated results are expected to align with the evolving landscape of digital health interventions in chronic disease management and prevention.

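### Section 3.9.2 gives the HADS total as 0 to 21, but its own 14 items sum to 0 to 42: a subscale range and its bands appear to be labelled as the total

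*Protocol article*

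**What the plan says.** The only scoring rule for the Hospital Anxiety and Depression Scale is in section 3.9.2 of the protocol article. It has four parts:

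- Number of items: the scale "consists of 14 items".
- Item scoring: "Each item offers four response options, scored from 0 to 3".
- Range and normal band: "The total score ranges from 0 to 21, with 0 to 7 indicating a normal range".
- Abnormal band: "scores from 8 to 21 are indicative of borderline or clinical concerns about anxiety or depression".

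The same section reports, as evidence of validity in Colombia, that "confirmatory factor analysis supported a satisfactory two-factor structure". It does not say how many items belong to each factor, or that the factors are scored separately.

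Section 4 (Expected Results) refers to the outcome in the plural: "we predict a reduction in anxiety and depression scores, as measured by the HADS". It gives no scoring rule, and no other section does.

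**The concern.** A scoring rule should let two analysts who work independently derive the same variable from the same item responses. This one does not. The stated range does not follow from the stated items, and the cut-off between 7 and 8 is attached to the quantity whose range is wrong.

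Two things are left open: whether the secondary outcome is one 14-item score or two separate scores, and which of these the bands belong to. An analyst who takes the word total literally would sum all 14 items and classify the sum with bands that stop at 21. That would label some participants abnormal although each half of their questionnaire lies in the normal band. It would also put anxiety and depression into one number, although section 4 discusses anxiety in its own right: greater awareness might raise it, and the support given is expected to lower it.

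**Working it through.** **Inputs, all from section 3.9.2:** 14 items; item minimum 0; item maximum 3; stated total 0 to 21; bands 0 to 7 and 8 to 21.

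**Step 1. Try to reproduce the stated range.** A sum score runs from (items × item minimum) to (items × item maximum).

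- 14 × 0 = 0 and 14 × 3 = 42. The total is 0 to 42, so the stated maximum of 21 is not reproduced.

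**Step 2. Find what would give 21.**

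- With 14 items, the item maximum would have to be 21 / 14 = 1.5. That contradicts the stated 0 to 3.
- With an item maximum of 3, the number of items would have to be 21 / 3 = 7, which is half the scale. The two bands, 0 to 7 and 8 to 21, then cover the range with no gap.

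So 21 fits one of two 7-item halves. The equal split is an assumption: the article reports two factors but not the number of items in each.

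**Step 3. Apply the bands to the 14-item sum.**

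- The sum can take 43 values (0 to 42). The bands cover 22 of them (0 to 21). The other 21 values (22 to 42) have no classification.
- Assume two 7-item halves. A participant with 4 on each half is in the normal band on both, but 4 + 4 = 8 falls in the abnormal band.
- The highest sum with both halves in the normal band is 7 + 7 = 14.
- There are 8 × 8 = 64 score pairs with both halves between 0 and 7. Those summing to 7 or less number 8 + 7 + 6 + 5 + 4 + 3 + 2 + 1 = 36, so 64 − 36 = 28 pairs sum to 8 or more. This counts possible pairs; it does not estimate how many participants would be affected.

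**Step 4. What cannot be computed.** The proportion misclassified would depend on the mean and standard deviation of each half and on their correlation. The article gives none of these, so no percentage is offered. For scale only: with 16 participants per arm (section 3.4), one participant moved across the cut-off changes that arm's proportion by 1 / 16 = 6.25 percentage points.

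**The case against.** The best defence is that this is a slip of wording over sound intended scoring. The bands fit a 0 to 21 score exactly and cannot serve a 0 to 42 sum. The section cites two factors, the abnormal band is described in terms of anxiety or depression, and section 4 speaks of scores in the plural. All of this points to a per-subscale range mistakenly called the total. This stands as the most probable explanation. It does not remove the defect, because the article nowhere says that the range or bands apply to each subscale.

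Three stronger readings are tempting, and the document does not support them.

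- **A reader might infer that the trial will report an inflated proportion of anxious or depressed participants.** Section 3.11 commits to no analysis of the proportion above the cut-off. It mentions frequency tables for categorical variables only in general, and section 4 predicts a fall in scores. Misclassification follows only if the bands are applied to the sum.
- **A reader might infer that anxiety and depression can no longer be assessed separately.** Section 3.9.2 describes an instrument and does not commit the analysis to one merged number. All 14 items are collected, so separate scores remain derivable.
- **A reader might infer that the trial's main conclusion is at risk.** HADS is a secondary outcome. The primary outcome is the knowledge score (section 3.8), and the sample size was calculated on the main outcome (section 3.10).

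**Conclusion.** The contradiction is certain and internal to section 3.9.2: the items give a maximum of 42, the text gives 21, and nothing elsewhere corrects it. This is an error in a stated rule, so it is not a detail that an article may leave to a fuller document.

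That a subscale range was labelled as the total is an inference, though a well-supported one. The illustration with 4 on each half, and the count of 28 pairs in 64, rest on an assumed 7/7 split. The gap at totals of 22 to 42 needs no such assumption.

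The severity is moderate. The practical risk is that a secondary outcome is scored or classified inconsistently, and it disappears once the rule is corrected before scoring.

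**What to change.** Before any HADS data are scored, correct section 3.9.2 as follows:

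1. Define two separate scores, anxiety and depression, each the sum of its own 7 items with a range of 0 to 21. Name the items in each, since the article does not give the split.
2. Apply the stated bands (0 to 7 and 8 to 21) to each score separately.
3. Analyse the two scores as two secondary outcomes. This agrees with the two-factor structure cited in section 3.9.2 and the plural wording in section 4.
4. If a 14-item total is also reported, give its range as 0 to 42 and do not apply these bands to it.

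The cost is about two sentences of text and a check of the scoring syntax. Data collection and the sample size do not change.

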#### 3.9.3. Quality-of-Life Score

The Short Form-36 Health Survey (SF-36) will be employed for this assessment. In Colombia, it has been validated in healthy individuals and those with chronic pain, diabetes, or depression, showing a test–retest reliability of above 0.70 [31] and exhibiting a robust inter-rater reproducibility with an intraclass correlation coefficient of 0.80 [31]. The SF-36 questionnaire consists of 36 items evaluating both positive and negative health states across eight domains: physical functioning, role–physical, bodily pain, general health, vitality, social functioning, role–emotional, and mental health [32].

### 3.10. Sample Size Calculation

The sample size was calculated considering the main outcome and a test for a comparison of means. This was based on the mean and standard deviation obtained in a previous study carried out by Tang et al. (2018) [19], a power of 80%, a significance level of 5%, and a 1: 1 ratio. Additionally, we doubled the sample size, anticipating possible losses to follow-up. The calculation was performed using the statistical software STATA 16.1. The result obtained was 16 participants per study group.

### 3.11. Statistical Analysis

Descriptive statistics such as means and standard deviations or medians and interquartile ranges for continuous variables and frequency tables for categorical variables will be used.

The bivariate analysis will be carried out to evaluate the differences in the variables measured within each group and between the study groups using parametric or non-parametric tests.

To evaluate the changes through follow-up, a repeated-measures analysis of variance will be applied if data follow a normal distribution, or a non-parametric variance analysis (ATS) if data do not follow a normal distribution [33]. Multivariable generalized estimating equation (GEE) models [34] will be applied to determine the effects of group, time, and the interaction between group and time on physical activity levels.

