## Abstract

Although the effectiveness of cardiac rehabilitation (CR) programs in secondary prevention is well-recognized, there is a lack of studies exploring the potential of mobile health to enhance educational interventions within CR. The objective is to assess the impact of a structured WhatsApp-assisted health educational intervention, in conjunction with the usual care, compared to the usual care alone among participants enrolled in a CR program. The trial will recruit 32 participants enrolled in a CR program, who will be randomly assigned to a structured WhatsApp-assisted health educational intervention plus usual care or usual care alone group. The intervention will span 4 weeks, with assessments at baseline, 4 weeks, and 3, 6, and 12 months. The primary outcome measure is the cardiovascular risk factors knowledge score. Secondary outcomes include physical activity levels, anxiety and depression, and quality of life. Expected results include improved knowledge of cardiovascular risk factors, increased physical activity levels, and better mental health outcomes in the intervention group. Additionally, an enhancement in the overall quality of life is anticipated. These findings are expected to underscore the value of integrating mHealth with traditional CR methods, potentially shaping future approaches in chronic disease management and prevention.

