### 3.2. Randomization and Masking

Randomization will be conducted after baseline assessment. The participants will be randomized into one of the two groups: WhatsApp-assisted health educational intervention with the usual care (intervention group) or the usual care (control group). We will employ permuted block randomization for participant allocation. This approach involves generating a randomized sequence using varying block sizes to assign participants to different treatment groups. This method ensures balanced group sizes and minimizes selection bias. To maintain methodological quality and safeguard this study’s integrity, an allocation concealment strategy will be utilized involving the use of sealed opaque envelopes. These envelopes will be sequentially numbered and prepared by an individual not involved in the enrollment or assessment of participants. They will only be opened by personnel separate from the envelope preparation and assessment processes, thereby maintaining the concealment of the allocation sequence until assignment and preventing potential biases. Evaluators and data analysts will be masked to treatment allocation; however, participants will not be masked. Furthermore, the evaluator responsible for initial assessments will be blinded to group assignments, ensuring an unbiased evaluation process. The therapist administering the intervention via WhatsApp will be different from the one providing usual care, reinforcing the independence of treatment delivery from the assessment process. This structure is designed to maintain the integrity of the study by separating roles and concealing group assignments from those conducting assessments. All team members involved in this study were trained on the importance of maintaining blinding and will be regularly monitored for compliance.

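### Section 3.11 states no baseline-adjusted between-arm contrast for the knowledge score, HADS or SF-36, and it plans within-arm tests that cannot show an effect of WhatsApp

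*Protocol article*

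**What the plan says.** Section 3.11 (Statistical Analysis) has three layers.

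- **Bivariate tests:** "The bivariate analysis will be carried out to evaluate the differences in the variables measured within each group and between the study groups", parametric or non-parametric. No covariate is named.
- **Change over follow-up:** "a repeated-measures analysis of variance will be applied if data follow a normal distribution, or a non-parametric variance analysis (ATS") otherwise. No group term or between-arm contrast is stated.
- **GEE:** multivariable models "to determine the effects of group, time, and the interaction between group and time on physical activity levels". No other outcome is named for these models.

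The Abstract makes knowledge the primary outcome ("The primary outcome measure is the cardiovascular risk factors knowledge score") and sets the schedule, "with assessments at baseline, 4 weeks, and 3, 6, and 12 months". Section 3.2 adds "Randomization will be conducted after baseline assessment", so the baseline score cannot be affected by allocation and is a valid covariate. Section 3.10 sizes the trial on an unadjusted comparison: "The sample size was calculated considering the main outcome and a test for a comparison of means".

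**The concern.** There are two linked problems.

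**Between arms.** Each outcome is measured before allocation, but the stated between-arm test for CRFK, HADS and SF-36 does not use that measurement. The planned ANOVA or ATS can take baseline in as one of its time points. The comparison of arms then behaves like a comparison of change scores, which is less precise than adjusting for baseline. Physical activity, a secondary outcome, has a stated group-by-time model; the primary outcome does not. With 16 per arm, avoidable variance matters.

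**Within arms.** Sections 3.4 and 3.4.1 give both arms supervised exercise and in-person education, so improvement in both is plausible. A p-value for change inside one arm does not measure what WhatsApp adds. Two such p-values can easily fall on opposite sides of 5% when the arms do not differ, and that pattern can be mistaken for a treatment effect.

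**Working it through.** **Inputs.** From the article: 16 per arm (Sections 3.4 and 3.10) and "a power of 80%, a significance level of 5%, and a 1: 1 ratio". Assumed, because the documents do not give them: a two-sided test, a true effect d of 0.8 SD, a baseline-to-follow-up correlation r of 0.3, 0.5 or 0.7, equal variances at both times, and complete data.

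**1. The plan's own figure.** The sample was doubled for losses, so the calculation gave 16/2 = 8 per arm. The mean difference and SD are not stated, so this cannot be reproduced forwards. Solved backwards with n = 2(1.96 + 0.84)²/d², 8 per arm implies d from 2.80 × √(2/8) = 1.40 to 2.80 × √(2/7) = 1.50, or 1.51 to 1.63 with the t distribution. That is possible and is not shown to be wrong. At 16 per arm, an unadjusted t test has 80% power at d = 1.02.

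**2. Precision of three between-arm comparisons.** In units of the follow-up variance, V is:

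- follow-up score alone: 1
- change score: 2(1 − r)
- ANCOVA: (1 − r²) × (1 + 1/(2n − 4)), which is (1 − r²) × (1 + 1/28) here; the second factor is the small-sample cost of estimating the slope

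The noncentrality is d × √(n/(2V)). Power is the noncentral t probability above the critical value: 2.042 on 30 df, or 2.045 on 29 df for ANCOVA.

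Follow-up score alone: 0.8 × √8 = 2.26, power 59%, whatever r is.

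| r | Change: V | noncentrality | power | ANCOVA: V | noncentrality | power |
|---|---|---|---|---|---|---|
| 0.3 | 1.40 | 1.91 | 46% | 0.91 × 1.036 = 0.94 | 2.33 | 62% |
| 0.5 | 1.00 | 2.26 | 59% | 0.75 × 1.036 = 0.78 | 2.57 | 70% |
| 0.7 | 0.60 | 2.92 | 81% | 0.51 × 1.036 = 0.53 | 3.11 | 85% |

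The gain from ANCOVA over the follow-up test is about 2 points at r = 0.3 (61.5% against 59.1%), 11 at 0.5 and 26 at 0.7. Over the change score it is 16, 11 and 4 to 5 points.

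**3. Within-arm tests when the arms do not differ.** Let both arms truly change by the same standardised amount c (mean change divided by the SD of change). With n = 16, the paired t test in each arm has noncentrality c × √16 = 4c, 15 df and critical value 2.131. If p is its power, the chance that exactly one arm is significant is 2p(1 − p).

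| c | p | 2p(1 − p) |
|---|---|---|
| 0.3 | 0.203 | 32% |
| 0.5 | 0.465 | 50% |
| 0.7 | 0.745 | 38% |
| 1.0 | 0.962 | 7% |

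By symmetry, the single significant arm is the WhatsApp arm in half of these cases. A valid between-arm test would be wrong 5% of the time in the same situation. The 50% is the maximum of 2p(1 − p), reached near p = 0.5.

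**The case against.** **Baseline is not ignored.** A reader might infer that the baseline score is thrown away and that unadjusted tests are the only comparison. Section 3.11 does not support that. Baseline can enter the repeated-measures ANOVA or ATS as a time point, and physical activity has a GEE with group-by-time. This stands, and it is why the concern is limited to CRFK, HADS and SF-36. It does not remove the concern: no group contrast is stated for the ANOVA or ATS, and the change-score behaviour that results is less precise than ANCOVA at every r in the table.

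**Covariates may be left to an analysis plan.** A condensed article need not list them, so silence alone would be no fault. The article is not merely silent, though. It commits to bivariate between-arm tests and to within-arm tests, and reserves the multivariable model for one secondary outcome.

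**The unadjusted test is valid.** This is correct. Randomisation keeps it unbiased with the right type I error, so the loss is one of precision.

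**The sizes rest on assumptions.** This is also correct. Neither r nor the 0.8 SD is in the documents. The benefit is small against the follow-up test at low r and against the change score at high r. The one-arm-only risk nearly vanishes if both arms change by 1 SD or more.

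**Misuse is speculative.** Section 4 frames the expected knowledge result against the control group, and nothing says that conclusions will rest on within-arm p-values. This stands: the plan leaves that route open but does not commit to it.

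**Conclusion.** The concern holds in limited form and is worth acting on, though it is not fatal. Section 3.11 states no baseline-adjusted between-arm contrast for the primary outcome, HADS or SF-36, and it plans within-arm tests that do not assess the effect of WhatsApp.

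The precision at stake ranges from slight to large depending on an unknown correlation. It also depends on whether the bivariate follow-up test or the ANOVA would be taken as decisive, which the article does not say. The within-arm risk is substantial for moderate equal improvement in both arms and small for large improvement.

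It would go too far to call the planned comparison biased or the sample size wrong; neither follows from the documents. All figures assume complete data at 16 per arm, and losses would lower every power shown.

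**What to change.** In Section 3.11, or in the analysis plan:

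- **Between arms:** compare CRFK, HADS and SF-36 with adjustment for the baseline score. Use ANCOVA at 4 weeks, or a longitudinal model (such as the GEE already planned for physical activity) with group, time, their interaction and baseline as a covariate. If data are clearly non-normal, use a rank-based ANCOVA.
- **Within arms:** drop the hypothesis tests. Report change as an estimate with its confidence interval.
- **Conclusions:** base them on the between-arm contrast alone.

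The cost is a change of wording and one degree of freedom per model. The data are already scheduled and the sample size is unaffected. If GEE is chosen, 32 participants are few for its robust standard errors, so a small-sample correction should be named.

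### GEE for physical activity with at most 16 participants per arm needs a small-sample variance and t/F reference; an uncorrected sandwich puts the joint group-by-time test at about 9-14%, not 5%

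*Protocol article*

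**What the plan says.** Section 3.11 assigns GEE to one outcome: "Multivariable generalized estimating equation (GEE) models [34] will be applied to determine the effects of group, time, and the interaction between group and time", completed by the words "the interaction between group and time on physical activity levels". The Abstract places that outcome among the secondary ones: "Secondary outcomes include physical activity levels, anxiety and depression, and quality of life". It also sets the schedule, "with assessments at baseline, 4 weeks, and 3, 6, and 12 months", which makes five occasions and therefore 4 interaction degrees of freedom if time is categorical.

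Section 3.10 gives the size: "The result obtained was 16 participants per study group". That figure already includes an allowance: "Additionally, we doubled the sample size, anticipating possible losses to follow-up". The calculation before doubling therefore required 8 per arm.

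The article names no variance estimator, working correlation, link, time coding or reference distribution for the GEE. Stata is mentioned only for the sample size. Section 3.11 also plans simple between-group tests, and repeated-measures ANOVA or a non-parametric counterpart for change over follow-up.

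**The concern.** GEE inference is justified by a large number of independent units. Here the units are participants, 32 at most. At that size the sandwich variance is biased downwards, and a chi-square reference ignores the uncertainty in estimating it. The joint interaction test suffers most, because it inverts an estimated 4 x 4 covariance matrix.

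The article expects physical activity to rise in the intervention group (section 4), and the Introduction names the 12-month comparison as an aim. An inflated test could supply that finding by chance. Unweighted GEE also generally needs data missing completely at random, in a trial that doubled its sample as a precaution against loss.

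**Working it through.** **Inputs.** n = 16 per arm, or 8 before doubling (section 3.10); five assessments (Abstract); nominal level 5% (section 3.10). Assumed, because not stated: continuous outcome, identity link, categorical time, true correlation 0.5 unless noted.

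**The plan's own figure.** The sample size was set for "a power of 80%, a significance level of 5%, and a 1: 1 ratio", with mean and SD from a cited study but not given, so 16 cannot be reproduced. Back-solving n = 2(1.96 + 0.84)²/d² with n = 8 gives d = √(2 × 7.85/8) = 1.40. The article states no type I error for the GEE.

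**Joint test, uncorrected sandwich, complete normal data.** With categorical time and no covariates, the GEE estimates are the arm-by-assessment means. The sandwich divides by n instead of n − 1. The Wald statistic is then W = [n/(n − 1)]T², where T² is the two-sample Hotelling statistic on the four changes from baseline. With N = 2n, T²(N − 5)/[4(N − 2)] follows F(4, N − 5). The chi-square cut-off is 9.488.

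- n = 16: 9.488 × 15/16 = 8.895; × 27/120 = 2.001; P(F(4,27) > 2.001) = 12.3%.
- n = 8: 9.488 × 7/8 = 8.302; × 11/56 = 1.631; P(F(4,11) > 1.631) = 23.5%.

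These values do not depend on the true correlation.

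**Simulation** (4,000 runs per scenario; Monte Carlo standard error about 0.3-0.7 percentage points):

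| Uncorrected sandwich | 16 per arm | 8 per arm throughout |
|---|---|---|
| Joint test, normal | 12.4-13.7% | 22.8-24.3% |
| Joint test, lognormal | 9.4% | 20.9% |
| Single-df interaction (one assessment or linear time) | 5.4-8.0% | 7.5-9.4% |

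The normal rows include decaying correlation and three added covariates. A packaged GEE routine (1,200 runs) gave 13.0% and 24.0% for the joint test. With monotone loss of 16, 14, 12, 10, 8 per arm across the five assessments and all available data used, the joint test rejects 15.5% and the 12-month contrast 7.7%.

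**Single contrast, exact.** Reject when |t| with N − 2 df exceeds 1.96√[(n − 1)/n]: 1.898 on 30 df gives 6.7%; 1.833 on 14 df gives 8.8%.

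**Model-based errors.** With a correct exchangeable structure the joint test holds: 5.4% at 16 and 4.7% at 8. If correlation decays but exchangeable is assumed, the true variance of the baseline-to-12-month contrast exceeds the modelled one by R = (1 − ρ₁₅)/(1 − mean ρ), and the large-sample rejection rate is P(|Z| > 1.96/√R):

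- AR(1) by assessment, 0.5: R = 0.9375/0.6938 = 1.351; 9.2%.
- AR(1) by assessment, 0.7: R = 0.7599/0.4804 = 1.582; 11.9%.
- Calendar-time decay, 0.7 per three months: R = 0.7599/0.4538 = 1.674; 13.0%.

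Simulation at the trial's size gives 10-14% (16 per arm) and 9.5-14% (8 per arm) with normal data, and 7-12% with lognormal. The 4-week contrast errs the other way, at 0-2%. With an independence working correlation and model-based errors, the joint test at 8 per arm rejects only 0.2%.

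**After correction.** In this design Mancl-DeRouen gives W = [(n − 1)/n]T². Comparing W/4 with F(4, N − 2):

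- n = 16: 4 × 2.690 × 16/15 = 11.476; × 27/120 = 2.582; 6.0%.
- n = 8: 4 × 3.112 × 8/7 = 14.227; × 11/56 = 2.795; 8.0%.

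Simulation gives 3.4-6.4% and 4.9-7.9%. Both parts are needed: by the same formula, Mancl-DeRouen with chi-square gives 8.7% and 14.5%, and the uncorrected sandwich with F gives 8.8% and 14.4%. Kauermann-Carroll gives W = T², so F(4, N − 2) yields 7.3% and 10.8%; the scaled F(4, N − 5) above is exact in this case. Single contrasts with Mancl-DeRouen and t ran at 3.8-5.3% (16) and 2.4-3.8% (8).

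**The case against.** The strongest objection is that the article never says sandwich errors will be used. Estimator, working correlation and reference distribution are commonly left to an analysis plan, which is not shown, and silence on them is no error. This stands, and it makes every figure above conditional. It does not remove the point: the article does fix GEE, five assessments and at most 32 participants, and at that size both standard large-sample versions can go wrong.

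A reader might infer that the group-by-time analysis as a whole will reject two to five times too often. The documents do not support that. The range belongs to the joint categorical-time test with an uncorrected sandwich and chi-square reference; single-df tests are inflated about 1.1-1.9 times, and lognormal data at 16 per arm give just under two-fold. The five-fold end needs only 8 per arm at every assessment. Randomisation follows baseline assessment (section 3.2) and GEE keeps the earlier records of those lost later, so gradual loss gives about three-fold. Doubling is a safety margin, not a forecast that half will leave.

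A reader might also extend the point to the knowledge score. Section 3.11 names GEE only for physical activity, and it plans other comparisons that do not exclude that outcome.

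**Conclusion.** The point holds in conditional form, for a secondary outcome. With an uncorrected sandwich and chi-square reference, the joint interaction test has about 9-14% type I error at 16 per arm, about 15% with gradual loss to 8, and about 21-24% with 8 throughout. Single contrasts run at about 5-9%, so confidence intervals at individual assessments are only modestly too narrow. Model-based errors are no general escape: they hold about 5% under the right working correlation, but the 12-month contrast rejects roughly 7-14% under plausible decay.

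This rests on a continuous outcome, categorical time for the joint test, and assumed correlation patterns. The exact calculation for complete normal data needs no correlation assumption and agrees with the simulations. It is a worthwhile, inexpensive improvement and does not put the primary analysis in doubt.

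**What to change.** In section 3.11, or the analysis plan it summarises, state for the physical activity GEE: the working correlation, categorical time, a bias-corrected variance, and t and F references in place of z and chi-square. Mancl-DeRouen with F(4, N − 2) brings the joint test to about 3-8%. If Kauermann-Carroll is preferred, pair it with the scaled F(4, N − 5), since F(4, N − 2) leaves 10.8% at 8 per arm.

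Alternatively, analyse the IPAQ score, transformed if skewed, with a likelihood-based mixed model for repeated measures and Kenward-Roger degrees of freedom. This needs only missing-at-random data. It was not simulated here, and it would be a new element, since the plan contains no mixed model to reuse.

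The cost is one sentence and a software option; no participants or assessments are added. With Mancl-DeRouen and t, intervals widen by (16/15) × (2.042/1.960) = 1.11 at 16 per arm and (8/7) × (2.145/1.960) = 1.25 at 8 per arm, where single contrasts become somewhat conservative.
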